#### Suspected unexpected serious adverse reactions (SUSAR)

A SUSAR is an unexpected and serious AE with presumed relation to the investigational drug. The term ‘unexpected’ is defined using the Byetta® Summary of product characteristics (http://www.ema.europa.eu/docs/en_GB/document_library/EPAR_-_Product_Information/human/000698/WC500051845.pdf), current as of 19 January 2014, as the reference document. The primary investigator as sponsor is responsible to report all serious (fatal or life threatening) SUSARs to the Danish Health and Medicines Authority as soon as possible and no later than 7 days after having been made aware of such an event. For all other SUSARs, the Danish Health and Medicines Authority must be informed as soon as possible and no later than 15 days after the sponsor has been made aware of the event.

All AEs, SAEs and SUSARs will be recorded and evaluated by the sponsor. The AEs will be reported in the electronic AE form no later than 24 hours from awareness of the AE. Each SAE and SUSAR requires that the investigator fill in the AE form, which is included in the CRFs. The following variables will be recorded: description of the event, onset and end of the event, severity, relation to intervention, action taken and outcome. Any AE occurring during the trial will be treated according to established standards, and the patient will be followed until the event has disappeared or until the condition has stabilised.

### Sample size estimation

The primary outcome is feasibility and the area under the NSE curve (NSE AUC) at 72 hours. Since no difference in feasibility is expected and the trial is designed as a pilot study, we have chosen to power this study according to differences in the NSE AUC. A difference of 20 % is defined as the minimal clinically relevant difference. Previous studies have found a value of approximately 20 μg/ml (25–75 % CI 10–45) at 72 hours [21]. We expect a mean AUC at 72 hours of 50 μg/ml*day, assuming an SD of 30 % of the mean AUC. The α is set at 0.025 (co-primary endpoint), which gives a power of 90 % if 50 patients are included in both groups. A 10 % loss of final measurement is expected (patients expiring before full 72 hours). Therefore, we aim to include 120 patients in total.

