### Statistical analysis plan

#### General principles

The general principles for statistical analyses will be:Analyses will be performed according to the intention-to-treat principle with patients lost to follow-up included in the denominator [22].A two-sided significance level of 0.025 will be applied to the primary endpoints and 0.05 will be applied to the secondary endpoints.The two trial sites will be asked to complete all CRFs and other forms if missing data is found in the electronic database. Missing data will be reported in the publication.More than 5 % missing data in outcome variables (see Endpoints) will result in multiple imputation with the creation of 10 imputed datasets to be analysed separately and then aggregated into one estimate of the intervention’s effect on the primary and secondary endpoints [23, 24].

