#### Analysis of endpoints

##### Primary outcome

The primary outcome of feasibility will be reported as the absolute percentage (with 95 % confidence interval) of patients in whom the study drug administration was initiated within 240 minutes of ROSC and the proportion in whom the study drug infusion was completed. The difference in NSE AUC between treatment groups will be tested with the independent-sample *t* test after logarithmic transformation (log2) to approximate a normal distribution. Missing NSE values will be imputed.

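### The 90 % power for NSE AUC rests on an SD of 30 % of the mean that is not reconciled with the far wider NSE spread quoted beside it, and the plan's own inputs give about 85–86 %

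*Protocol article*

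**What the plan says.** All the inputs are in the protocol article.

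- Sample size estimation, target effect: "A difference of 20 % is defined as the minimal clinically relevant difference".
- Same section, prior data: "Previous studies have found a value of approximately 20 μg/ml (25–75 % CI 10–45) at 72 hours". The label is read here as an interquartile range.
- Same section, assumed mean: "We expect a mean AUC at 72 hours of 50 μg/ml*day", followed by "assuming an SD of 30 % of the mean AUC". No link is drawn between this SD and the quartiles just before it.
- Same section, error rate and power: "The α is set at 0.025 (co-primary endpoint"), "which gives a power of 90 % if 50 patients are included in both groups". After allowing for 10 % without a final measurement, the target is 120 patients in total.
- General principles: "A two-sided significance level of 0.025 will be applied to the primary endpoints".
- Primary outcome: the groups are compared with an independent-sample t test "after logarithmic transformation (log2) to approximate a normal distribution".

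**The concern.** Quartiles of 10 and 45 around 20 are right-skewed and 4.5-fold apart. A CV of 30 % around 20 would put the quartiles near 16 and 24. The AUC averages several samples from one patient and may vary less than a single sample, but the text does not explain how a CV above 100 % at 72 hours becomes 30 % for the AUC. The power figure depends heavily on that step.

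The figure matters because NSE AUC is the efficacy co-primary endpoint, and the Discussion (Surrogate endpoints) gives adequate power as the reason for choosing a surrogate. If the AUC varies more than assumed, a null result could be compatible with the 20 % reduction that the plan calls relevant, while a stated 90 % power would encourage the opposite reading.

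**Working it through.** **Inputs.** From the documents: difference 20 % (10 on a mean of 50; ratio 0.80 on the log scale), SD 0.30 × 50 = 15, two-sided alpha 0.025, 50 per arm. N = 120 gives 60 per arm, or 60 × 0.9 = 54 evaluable. Assumed: log-normal NSE and AUC, the AUC CVs in step 3, and the correlations and early spreads in step 4.

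**1. The plan's own figure.** Standardised difference = 10/15 = 0.667. Normal approximation: power = Φ(0.667·√(n/2) − z), with z = 2.241 for two-sided 0.025. At n = 50 this is Φ(3.333 − 2.241) = Φ(1.092) = 86.3 %.

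| Per arm | Two-sided 0.025, t / normal | Two-sided 0.05, t / normal |
|---|---|---|
| 50 | 85.3 / 86.3 % | 91.0 / 91.5 % |
| 54 | 88.1 / 88.9 % | 93.0 / 93.4 % |
| 60 | 91.5 / 92.1 % | 95.2 / 95.5 % |

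On the raw scale with 50 per arm, 90 % is reached at two-sided 0.05 and not at the two-sided 0.025 in General principles. At 0.025 the normal approximation needs 56 per arm.

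**2. Spread implied by the quartiles.** Log-SD = ln(45/10)/(2 × 0.6745) = 1.504/1.349 = 1.115. Log-normal CV = √(exp(1.115²) − 1) = 1.57. Using only the lower or the upper half of the range gives 137 % or 180 %. A normal reading gives SD = 35/1.349 = 25.9, which is 130 % of 20, or 104 % of (10 + 20 + 45)/3 = 25. Every reading exceeds 100 %.

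**3. Power by AUC CV, on the scale of the planned test.** Log-SD s = √ln(1 + CV²); standardised effect = |ln 0.80|/s = 0.223/s; t test, two-sided 0.025. The ratio detectable with 90 % power is exp(−d·s), with d = 0.714 at 50 per arm and 0.650 at 60.

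| AUC CV | s | Power for ratio 0.80 (50 to 60 per arm) | Ratio detectable with 90 % power (50 to 60 per arm) |
|---|---|---|---|
| 30 % | 0.294 | 93–97 % | 0.81–0.83 |
| 40 % | 0.385 | 73–82 % | 0.76–0.78 |
| 50 % | 0.472 | 54–63 % | 0.71–0.74 |
| 75 % | 0.668 | 28–33 % | 0.62–0.65 |
| 100 % | 0.833 | 18–22 % | 0.55–0.58 |

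With 54 evaluable per arm, 90 % power for a ratio of 0.80 needs a CV of at most about 33 % (t) or 34 % (normal).

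**4. What the 72-hour spread could mean for the AUC (simulation, illustrative).**

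- *Same spread at every time.* Three equally weighted daily values, each with log-SD 1.115 and within-patient correlation 0.3–0.9: log-SD of the AUC 0.85–1.08, power 11–17 % with 50 per arm and 13–21 % with 60.
- *Narrower spread earlier.* Trapezoid over 0, 24, 48 and 72 hours, equal medians, log-SD 1.115 at 72 hours, same correlations. With earlier log-SDs of 0.3/0.3/0.3, 0.3/0.4/0.7 or 0.5/0.7/0.9, the AUC CV is about 49–98 % and power about 20–87 % (50–60 per arm).
- *No variation between patients before 72 hours.* Same trapezoid: log-SD of the AUC 0.27, and power stays above 90 %.

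**The case against.** The strongest objection is that the quartiles describe one concentration at 72 hours, while the endpoint is the area from admission to 72 hours. The documents give no spread for earlier samples or for the AUC, and no within-patient correlation. This stands. A reader might infer that the true power is 11–17 %. That range needs the 72-hour spread at every sampling time, which the documents do not say. That model also misses the plan's own mean: a log-normal with median 20 and log-SD 1.115 has mean 20 × exp(1.115²/2) ≈ 37, so three days give about 112 against the 50 expected. It is a pessimistic scenario, not an estimate.

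Three further points stand in part.

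- A reader might infer that planning on the raw scale and testing on the log scale in itself costs power. It does not: at a CV of 30 % the log-scale test has about 93.5 % power with 50 per arm, against 85.3 % on the raw scale. The reason to use the log scale is to match the planned test.
- A condensed article may leave the source of the 30 % to the full protocol. So the absence of a derivation is not the fault; the unexplained mismatch between two adjacent printed figures is.
- The trial calls itself a pilot, and nothing says that a null result will be read as no effect. But the article does print a formal power claim, and that claim should be correct.

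**Conclusion.** The point holds in conditional form. The 30 % SD is not reconciled with the only spread cited, and power falls quickly as the AUC CV rises above it: to about 54–63 % at 50 % and 18–22 % at 100 %. If the 72-hour spread applied throughout, power would be about 11–21 % (50–60 per arm, correlation 0.3–0.9 assumed). Every scenario with some narrower early variation stayed below 90 %. Only the limiting case of none before 72 hours reached it, so the documents do not strictly rule out 90 %; they give no support for it.

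The second part needs no outside assumption. With the plan's own SD and 50 per arm, the raw-scale power at two-sided 0.025 is about 85–86 %, or 88–89 % with the 54 evaluable that N = 120 provides. This gap is small and largely covered by the enrolment target. The variance assumption is the more important part.

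**What to change.** Keep N = 120 and rewrite the power statement in Sample size estimation.

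1. Do the calculation on the log scale of the planned test, for a ratio of 0.80, naming the two-sided alpha of 0.025 and the number evaluable per arm.
2. Justify the SD from AUC data, or explain how it follows from the quoted quartiles of 10 and 45.
3. Replace the single 90 % with power over a stated range of AUC CVs and the ratio detectable with 90 % power at each, as in the table in step 3. Do not print 11–17 %, or any other single figure borrowed from the 72-hour value, as the power of the trial.
4. State that a non-significant NSE result will be reported as a ratio with its confidence interval and will not be read as excluding a 20 % reduction.

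The cost is rewording and a search for AUC data, with no extra patients. The downside is that the stated power becomes less favourable.

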**Methods/design:**

This pilot study will randomize a total of 120 unconscious patients with sustained return of spontaneous circulation after out-of-hospital cardiac arrest undergoing targeted temperature management in a blinded one-to-one fashion to a 6-hour and 15-minute infusion of either Exenatide or placebo. Patients are eligible for inclusion if resuscitated from cardiac arrest with randomization from 20 minutes to 240 minutes after return of spontaneous circulation. The co-primary endpoint is feasibility, defined as the initiation of treatment within the inclusion window in more than 90 % of participants, and efficacy, defined as the area under the neuron-specific enolase curve from 0 to 72 hours after admission. Secondary endpoints include all-cause mortality at 30 days and Cerebral Performance Category as well as a modified Rankin Score at 180 days. The study has been approved by the Danish National Board of Health and the local Ethics Committee and is monitored by Good Clinical Practice units. The study is currently enrolling.

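### On the plain reading of the sample size paragraph, 50 per group gives about 85 % power at two-sided alpha 0.025, not the stated 90 %; the error is small and is corrected by restating the figure or its basis

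*Protocol article*

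**What the plan says.** The sample size section of the protocol article powers the trial on the area under the NSE curve alone. It fixes the effect: "A difference of 20 % is defined as the minimal clinically relevant difference". It fixes the mean and spread: "We expect a mean AUC at 72 hours of 50 μg/ml*day, assuming an SD of 30 % of the mean AUC". It then says that alpha "is set at 0.025 (co-primary endpoint), which gives a power of 90 % if 50 patients are included in both groups". On attrition it says "A 10 % loss of final measurement is expected" and arrives at 120 patients in total. The abstract gives the allocation as "in a blinded one-to-one fashion".

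The General principles section supplies the sidedness: "A two-sided significance level of 0.025 will be applied to the primary endpoints".

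The Primary outcome section plans a t test on log2-transformed values for NSE AUC. For the other co-primary endpoint it says "The primary outcome of feasibility will be reported as the absolute percentage", with a 95 % confidence interval. It plans no comparison between arms for feasibility.

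**The concern.** All the inputs needed to check the power statement are in the text, and on their plain reading they do not give 90 % at the declared level. They give it at two-sided 0.05. That pattern suggests that the level was lowered to 0.025 for the co-primary structure without the power being recalculated, although the document does not say how the figure was obtained.

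What is at stake is the accuracy of a stated design property. A reader who takes the article at its word expects a 10 % chance of missing a true 20 % difference with 50 per group. On the plain reading the chance is about 15 %. The validity of the planned test is not affected.

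**Working it through.** **Inputs**
- Mean 50, SD = 0.30 × 50 = 15, difference = 0.20 × 50 = 10 (Sample size estimation).
- 50 per group, alpha 0.025 (Sample size estimation); two-sided (General principles); 1:1 allocation (abstract).

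**Standardised effect and noncentrality**
- d = 10 / 15 = 0.667.
- Noncentrality = d × √(n/2) = 0.667 × √25 = 3.333.

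**Which level reproduces the stated 90 %?** By normal approximation, power = Φ(noncentrality − z), with z the two-sided critical value:
- two-sided 0.05: Φ(3.333 − 1.960) = Φ(1.373) = 91.5 %
- two-sided 0.025: Φ(3.333 − 2.241) = Φ(1.092) = 86.3 %

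The stated figure is met at two-sided 0.05 and missed at the declared level. The noncentral t distribution, which matches the planned type of test, gives the same picture:

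| n per group | two-sided 0.025 | two-sided 0.05 |
|---|---|---|
| 50 | 85.3 % | 91.0 % |
| 54 | 88.1 % | 93.0 % |
| 60 | 91.5 % | 95.2 % |

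The row for 54 is planned enrolment after the stated loss: 120 × 0.90 = 108, or 54 per group. The row for 60 is full enrolment with no loss.

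**Size needed for 90 %.** By normal approximation, n = 2 × (z for alpha + 1.282)² / d²:
- two-sided 0.025: 2 × (2.241 + 1.282)² / 0.444 = 55.9, so 56 per group (58 by t test)
- two-sided 0.05: 2 × (1.960 + 1.282)² / 0.444 = 47.3, so 48 per group (49 by t test)

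The stated 50 per group sits next to the second line, not the first.

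**Other bases that the paragraph does not state** (t test, 50 per group, two-sided 0.025):
- SD of 30 % of each arm's own mean, with means 50 and 40: SDs 15 and 12, pooled √((225 + 144)/2) = 13.6, d = 0.736, power 91.8 %.
- Log scale, 20 % reduction: effect −ln 0.8 = 0.223. With log SD √ln(1 + 0.30²) = 0.294, power is 93.5 %; with log SD 0.30 it is 92.4 %.
- Log scale, 20 % increase: effect ln 1.2 = 0.182. Power is 79.5 % with log SD 0.294 and 77.6 % with 0.30.

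The result therefore depends on scale and direction, and the paragraph specifies neither.

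**The case against.** The strongest counter-argument is that the planned test is on the log scale, while effect and spread are given as percentages. For a 20 % reduction, the direction that a neuroprotective hypothesis implies, the log-scale test has 92 to 93 % power at two-sided 0.025, so 90 % would be met. This stands in part: it prevents anyone from asserting that 85 % is the trial's true power. It does not rescue the sentence. The paragraph gives one SD tied to one expected mean and does not mention a log-scale calculation. If such a calculation was used, it should be stated.

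A second defence is that one-sided 0.025 equals two-sided 0.05 and reproduces the figure. The General principles section rules this out by specifying a two-sided level.

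A third is that 120 patients are enrolled, not 100, and that missing NSE values are imputed. This stands as a point about size: power is 88.1 % with 54 per group and nominally 91.5 % with 60. The sentence, however, attaches its 90 % to 50 per group.

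A reader might also infer that half of the alpha is reserved for feasibility and wasted, so that the NSE AUC test ought to go back to 0.05. The documents do not support that. No section sets out a split of 0.025 plus 0.025; it is inferred from the co-primary label. Feasibility does have a success threshold of more than 90 %, against which its interval can be read. A stricter level for efficacy is conservative and cannot inflate the type I error. What remains is an observation: feasibility is a pooled percentage with a 95 % interval and no between-arm test, so the co-primary rationale for 0.025 is weak.

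**Conclusion.** The power statement is wrong as written, and the error is minor. With a common SD of 15, a raw-scale difference of 10 and two-sided alpha 0.025, power is about 85 % with 50 per group, roughly 5 points below the stated 90 %. With the 54 per group expected after loss it is about 88 %, roughly 2 points below.

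The conclusion rests on reading the paragraph as a raw-scale calculation with a common SD, which is its plain sense but is not spelled out. All the figures also depend on the assumed SD of 30 % of the mean. A reader might infer that the trial is seriously undersized; on these inputs it is not. The fault lies in the pairing of the stated power with the stated alpha.

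**What to change.** Keep alpha at two-sided 0.025 and correct the sentence in the sample size section in one of two ways:
- restate the power as about 85 % for 50 per group and about 88 % for 54 per group; or
- if the calculation was made on the log scale or with arm-specific SDs, say so and give its inputs (scale, direction of the 20 % difference, SD in each arm), with the resulting power of about 92 to 93 % for a 20 % reduction.

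The cost is one sentence. It needs no extra patients or data and no change to the analysis.

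Testing NSE AUC at two-sided 0.05, with feasibility as a descriptive co-primary, is open to the sponsor but not required. It would relax the efficacy level in a trial already enrolling. The Data monitoring section plans a formal interim analysis that reviews efficacy, and the article shows no alpha adjustment for it. Any such change should be decided and documented before unblinding, and only after that interim look has been accounted for.

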### Statistical analysis plan

#### General principles

The general principles for statistical analyses will be:Analyses will be performed according to the intention-to-treat principle with patients lost to follow-up included in the denominator [22].A two-sided significance level of 0.025 will be applied to the primary endpoints and 0.05 will be applied to the secondary endpoints.The two trial sites will be asked to complete all CRFs and other forms if missing data is found in the electronic database. Missing data will be reported in the publication.More than 5 % missing data in outcome variables (see Endpoints) will result in multiple imputation with the creation of 10 imputed datasets to be analysed separately and then aggregated into one estimate of the intervention’s effect on the primary and secondary endpoints [23, 24].

#### Trial profile

A flowchart of the study participants will be displayed according to the Consolidated Standards of Reporting Trials (CONSORT) diagram [25] as Fig. 1.

#### Baseline data

The predefined baseline variables will be as follows:SexAgeComorbidities (pre-morbid CPC, NYHA class 3 or worse, previous myocardial infarction, ischemic heart disease, previous arrhythmia, previous cardiac arrest, arterial hypertension, transient ischemic attack or stroke, epilepsy, diabetes, asthma or chronic obstructive pulmonary disease, chronic haemodialysis or peritoneal dialysis, hepatic cirrhosis, haematological malignancy, other malignancy, AIDS, alcoholism, intravenous drug abuse, or other immunodeficiency)Previous percutaneous coronary interventionPrevious coronary artery bypass graftPrevious valvular surgeryImplantable cardioverter-defibrillator and/or pacemakerPre-hospital variablesLocation of cardiac arrestBystander witnessed arrestBystander CPRShockable primary rhythmTime to basic life supportTime to advanced life supportTime to ROSCAdmission variablesFirst measured temperatureGlasgow Coma ScoreShock at admissionST-elevation acute myocardial infarctionpHLactateCreatinine

Possible differences in baseline characteristics between the treatment groups will be analysed and displayed in Table 1. Continuous variables will be presented as mean ± SD, and differences will be analysed with the *t* test. In case of skewed data, continuous variables will be presented as median (inter-quartile range) and a *t* test will be applied following logarithmic transformation; secondarily, a non-parametric Mann-Whitney test will be applied. Categorical variables will be presented as *n* (%) and differences will be analysed with the chi-square test.

#### Analysis of endpoints

##### Primary outcome

The primary outcome of feasibility will be reported as the absolute percentage (with 95 % confidence interval) of patients in whom the study drug administration was initiated within 240 minutes of ROSC and the proportion in whom the study drug infusion was completed. The difference in NSE AUC between treatment groups will be tested with the independent-sample *t* test after logarithmic transformation (log2) to approximate a normal distribution. Missing NSE values will be imputed.

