### Endpoints

The co-primary endpoints are as follows:Feasibility, defined as > 90 % initiation of study drug administration within 4 hours following ROSC in patients eligible for inclusionEfficacy, defined as the area under the NSE curve from admission to 72 hours post-admission. Missing data will be imputed.

Secondary endpoints are as follows:Area under the S100B curve with daily measurements until 72 hours, and absolute NSE and S100B values at 48 hours. Missing data will be imputed.Composite outcome of all-cause mortality and poor neurological function, defined as the modified Rankin Scale (mRS) 4–6 at 30 days (telephone assessment)Vital status at 7 days and at least 180 days (end of the study) after OHCA by registry-based follow-upAssessment of CPC and mRS at 90 daysArea under the creatine kinase MB (CK-MB) and troponin T curve from 0 to 24 hours. Missing data will be imputed.Safety, defined as the cumulated incidence of serious adverse events (SAE) related to the study drug: death, need for mechanical hemodynamic support, hypoglycaemia < 3.0 mmol/l, pancreatitis (S-amylase > 3 UNL), need for renal replacement therapy in the first 3 days. In addition, hypoglycaemia and pancreatitis will be reported separately as additional safety.

Tertiary endpoints are as follows:Left ventricular ejection fraction on last in-hospital echocardiography, stratified by the presence of acute myocardial infarction as the cause of cardiac arrest. Patients dying during the index administration in whom a post-TTM echocardiography is not available will be given the lowest LVEF score seen in each allocation group. Missing data will be imputed.Presence of EEG findings associated with poor prognosis and EEG performed as part of per-protocol prognosticationVital status at 180 days and telephone-based CPC and mRS at 180 daysVital status at 180 days stratified for cause of death (i.e. neurological versus cardiovascular and other – will be adjudicated by two intensive-care consultants blinded to treatment allocation)

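### The feasibility co-primary is reported with a 95 % interval although the plan sets a two-sided 0.025 level for primary endpoints, and an observed rate just above 90 % should not be worded as a demonstrated one (minor)

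*Protocol article*

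**What the plan says.** Four places in the protocol article bear on this.

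- **Endpoints.** Feasibility is the first of two co-primary endpoints, "defined as > 90 % initiation of study drug administration" within four hours of ROSC. The abstract has "initiation of treatment within the inclusion window in more than 90 % of participants". Neither place attaches a confidence bound, a test or a null rate.
- **General principles.** "A two-sided significance level of 0.025 will be applied to the primary endpoints". The word is plural, and no exception is made for feasibility.
- **Sample size estimation.** The co-primary structure is given as the reason for the level: "The α is set at 0.025 (co-primary endpoint), which gives a power of 90 % if 50 patients are included in both groups". Feasibility is not used for sizing: "Since no difference in feasibility is expected and the trial is designed as a pilot study" introduces the decision to power on the NSE curve alone.
- **Primary outcome (Analysis of endpoints).** Feasibility is to be reported as the "absolute percentage (with 95 % confidence interval"). The following sentence plans a t test for the NSE area under the curve.

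**The concern.** The level and the interval do not match. If 0.025 two-sided governs both primary endpoints, the corresponding interval has 97.5 % coverage. The planned 95 % interval belongs to two-sided 0.05, so it is somewhat narrower than the plan's own level implies. Feasibility is also the endpoint whose co-primary status led to the lower level.

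The second part concerns what is concluded. The criterion is met by any observed rate above 90 %, and the article does not say how the interval enters the conclusion. If a result such as 109/120 were summarised only as feasibility having been met, a reader could take it as evidence that the true rate is above 90 %, which the interval would not support. At stake is the precision attached to a co-primary endpoint and the wording of its conclusion.

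**Working it through.** **Inputs.** Target: observed rate above 90 % (Endpoints). Level: two-sided 0.025 (General principles). Planned interval: 95 % (Primary outcome). Denominator: 120, from "Therefore, we aim to include 120 patients in total". The denominator is an assumption, because the abstract counts participants while the Endpoints section counts patients eligible for inclusion, and only the former points to 120. The article gives no power or precision figure for feasibility, so there is none to reproduce.

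**Step 1: matching the interval to the level.** Coverage = 1 − two-sided level. For 0.025 this is 97.5 %; for 0.05 it is 95 %. The lower limit of a 95 % interval is a one-sided 2.5 % bound, which corresponds to two-sided 0.05 and not to the stated two-sided 0.025.

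**Step 2: smallest result that meets the target.** 108/120 = 90.0 %, which is not above 90 %. 109/120 = 90.8 %, which is.

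**Step 3: exact (Clopper–Pearson) limits.** For x of n at two-sided level a, lower = Beta quantile (a/2; x, n − x + 1) and upper = Beta quantile (1 − a/2; x + 1, n − x).

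| Result | Observed | 95 % interval | 97.5 % interval |
|---|---|---|---|
| 109/120 | 90.8 % | 84.2–95.3 % | 83.2–95.8 % |
| 115/120 | 95.8 % | 90.5–98.6 % | 89.7–98.9 % |
| 116/120 | 96.7 % | 91.7–99.1 % | 90.9–99.3 % |

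At 109/120 the lower limit moves by 84.2 − 83.2 = 1.0 percentage point. The choice of level changes whether the lower limit lies above 90 % for one result only, 115/120.

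**Step 4: how often the target is met.** P(X ≥ 109) with X binomial (120, p):

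| True rate p | Probability of meeting the target |
|---|---|
| 90 % | 0.456 |
| 88 % | 0.211 |
| 86 % | 0.076 |
| 85 % | 0.042 |
| 83 % | 0.011 |

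A true rate at the target passes a little under half the time. The chance then falls quickly, to about one in five at 88 % and one in thirteen at 86 %.

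**The case against.** The strongest reply is that no test of feasibility is planned. The Primary outcome section says feasibility is reported and NSE is tested, a significance level governs tests, and the trial was sized on NSE alone. For a pilot, an observed rate as an operational target is a normal choice. The interval is printed beside the percentage, so a reader of 109/120 would see 84.2–95.3 %, and the uncertainty is disclosed. A condensed article may also leave a formal decision rule to the full protocol.

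Most of this stands. It rules out two stronger readings that a reader might infer:

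- *That the success rule and the 0.025 level contradict each other for every result from 109 to 115 of 120.* This needs a test against a 90 % null, or a rule that the lower limit must exceed 90 %. The article sets neither. The mismatch in level by itself matters only at 115/120.
- *That success should require at least 116/120.* This would be a new and severe rule. Its false-claim rate at a true 90 % would be 0.56 %, and its chance of success only 28 % at a true 95 % (71 % at 97 %, 91 % at 98 %). Nothing in the article calls for it.

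Nor can it be said that rates well below 90 % would often pass; Step 4 shows otherwise.

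What the reply does not remove is the literal mismatch. The general principles name the primary endpoints in the plural and say two-sided. Reading 0.025 as one-sided would make the 95 % interval fit, but the stated sidedness excludes that reading. If the level was meant for the NSE test alone, the sentence does not say so.

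**Conclusion.** The point holds in a limited form, as a minor one. Two sentences of the same analysis plan give different levels for the feasibility co-primary: two-sided 0.025 in the general principles, and a 95 % interval in the analysis of the endpoint. On the assumed denominator of 120 and exact binomial limits, the effect at the smallest passing result is about one percentage point at the lower limit.

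The observed-rate target is legitimate for a pilot. Meeting it is still not the same as showing a true rate above 90 %: at 109/120, true rates down to about 84 % lie within the 95 % interval, and down to about 83 % within the 97.5 % interval. A different denominator would change the counts but not the mismatch in level.

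**What to change.** In the Primary outcome section, report the feasibility percentage with an exact 97.5 % interval, in line with the general principles. Keep an observed rate above 90 % as the pilot's descriptive target. Add one sentence on wording: when the target is met but the lower limit does not exceed 90 %, the conclusion reads *target observed, lower confidence limit X %*; only when the lower limit itself exceeds 90 % is a rate above 90 % described as shown. Do not write a count such as 116/120 into the plan as a success threshold.

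The cost is two sentences of analysis text, with no change to patients, data or trial conduct. The downside is a slightly wider interval (about one percentage point at the lower limit for 109/120) and a more cautious conclusion.
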